### Statistical design overview

#### Sample size determination

In literature, discontinuation of adjuvant hormone therapy is reported in 20% of cases. The option of offering patients a web-application rather than an accompaniment by a standard follow-up would appear relevant if it allows to observe a difference in discontinuation rate of at least 10%. According to a two proportion z-test, with a two-sided alpha risk of 5% and a power of 80%, 398 patients (199 per arm) are required to observe a significant difference in the discontinuation rate of at least 10%, assuming an adherence failure rate of 20% in the control arm. To take into account a 10% drop-out rate, we plan to enroll 438 patients overall (219 per arm).

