The most commonly described ADRs are joint pain [8], sexual dysfunction [9] (with or without gynecological symptoms), weight increase, fatigue, mood disorders (up to anxiety-depression syndrome) and vasomotor symptoms (hot flashes and/or night sweats). ADRs have an impact on patients’ quality of life, but also on adherence to treatment [10, 11]. A study conducted among 8,769 patients treated with adjuvant hormone therapy observed a poor adherence rate of 37% and discontinuation of treatment in 20% of cases within the first year of hormone therapy [12]. Similarly, an observational study in United States showed that more than 30% of patients had discontinued AI two years after starting treatment [13]. The assessment of hormone therapy adherence in this study was based on the use of the Morisky scale© 2006 Donald E. Morisky. A study conducted in Singapore [14] reported that only 41% of 157 women were adherent to hormone therapy in the first 2 years: forgetting to take the treatment and avoiding the hormone therapy side effects were the main reported reasons for non-adherence.

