### Primary outcome

The main objective is to evaluate the benefit of the WEBAPPAC web-application on patient adherence to adjuvant hormone therapy for breast cancer 18 months after treatment start.

The primary endpoint of the study is the proportion of patients with adherence failure of hormone therapy within 18 months after treatment start, in each arm. Adherence failure of hormone therapy will be defined by at least one of the following items:

Adherence score less than 6 on the 8-item Morisky questionnaire (MMSA8) [22–25], completed at 18 months;Treatment discontinuation since at least one month, documented in the patient’s adherence notebook;Absence of hormone therapy dispensation for at least one month, documented on the hormone therapy prescription, with traceability of each dispensation noted on the prescription;Permanent discontinuation of hormone therapy as declared by the patient at the 18-month follow-up medical consultation.

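### The 80% power uses a 20% discontinuation rate as the control rate for a broader 18-month composite; at the more plausible 25–37%, power for 10 points is about 57–75%

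*Protocol article*

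**What the plan says.** The Sample size determination section of the protocol article starts from the statement that "discontinuation of adjuvant hormone therapy is reported in 20% of cases", with no time point or citation. It calls the application worthwhile if it produces "a difference in discontinuation rate of at least 10"%. It then sizes the trial "with a two-sided alpha risk of 5% and a power of 80"%, concluding that "398 patients (199 per arm) are required", "assuming an adherence failure rate of 20% in the control arm". Enrolment is raised to 438 (219 per arm) for 10% drop-out.

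The Primary outcome section defines the endpoint over 18 months: "Adherence failure of hormone therapy will be defined by at least one of the following items". The items are a Morisky score below 6 at 18 months, a treatment interruption of at least one month in the notebook, at least one month without dispensation, and permanent discontinuation declared at the 18-month visit.

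The Background (section on adverse effects and adherence) describes a cohort of 8,769 patients that "observed a poor adherence rate of 37% and discontinuation of treatment in 20% of cases within the first year of hormone therapy", and a United States study in which "more than 30% of patients had discontinued AI two years after starting treatment".

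The Statistical analyses section plans an intent-to-treat chi-squared test. Patients lost at 18 months take their 6-month adherence status. If that is missing, they count as non-adherent in the experimental arm and adherent in the control arm.

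**The concern.** Within one paragraph the sizing argument moves from discontinuation to adherence failure and keeps the same 20% for both. The only 20% discontinuation figure in the Background covers the first year of treatment. The endpoint runs six months longer and also counts patients who stay on treatment but score low on the Morisky scale or have a one-month gap. Other things equal, both features push the control rate upward, and the article gives no reason for holding it at 20%.

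This matters because the variance of a difference in proportions grows as the rates move from 20% towards 50%. A fixed 10-point difference becomes harder to detect. If the control rate is higher than planned, the trial has less than its stated power for the benefit it calls worthwhile, and a null result could be read as stronger evidence against the application than it is.

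**Working it through.** **Inputs.** Two-sided α = 0.05 (z = 1.960), power 80% (z = 0.842), control rate 20%, 199 per arm evaluable and 219 per arm enrolled, all from Sample size determination. Other control rates come from the Background figures, as set out in step 2.

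**Formulas** (pooled two-proportion z-test, no continuity correction; p̄ is the mean of p₁ and p₂):

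- n per arm = [1.960·√(2p̄(1−p̄)) + 0.842·√(p₁(1−p₁)+p₂(1−p₂))]² / (p₁−p₂)²
- power = Φ{ [(p₁−p₂)·√n − 1.960·√(2p̄(1−p̄))] / √(p₁(1−p₁)+p₂(1−p₂)) }

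**Step 1: reproduce the plan.** For 20% v 10%, p̄ = 0.15, √(2·0.15·0.85) = 0.505 and √(0.16+0.09) = 0.500. So n = (1.960·0.505 + 0.842·0.500)²/0.01 = 198.96, rounded up to 199 per arm (398). The plan's figure is reproduced exactly. This also shows that the 10% was used as an absolute difference.

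**Step 2: a plausible range for the control rate.** The article gives no 18-month rate for the composite, so the range is an assumption.

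- Lower end, about 25%: midway between 20% discontinuation at one year and 30% at two years, (20+30)/2 = 25% at 18 months. This counts discontinuation only and joins two different cohorts.
- Upper end, 37%: poor adherence in the cohort that also had 20% discontinuation.

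**Step 3: power for a 10-point absolute difference.** Worked case at 30% v 20%, n = 199: p̄ = 0.25, √(2·0.25·0.75) = 0.612, √(0.21+0.16) = 0.608 and 0.10·√199 = 1.411. Power = Φ[(1.411 − 1.960·0.612)/0.608] = Φ(0.346) = 63.5%.

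| Control v experimental | Power, 199 per arm | Power, 219 per arm |
|---|---|---|
| 20% v 10% | 80.0% | 83.7% |
| 25% v 15% | 70.5% | 74.6% |
| 30% v 20% | 63.5% | 67.7% |
| 37% v 27% | 57.1% | 61.2% |

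The last column applies if everyone randomised is analysed. It takes no account of imputation, which counts patients with no adherence data against the application and so shrinks the expected difference.

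**Step 4: difference detectable with 80% power, 199 per arm** (power formula solved for the difference): 10.0 points at 20%, 11.1 at 25%, 12.0 at 30%, 12.9 at 37%.

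**Step 5: a relative effect instead.** If the application halves failure whatever the base rate, power with 199 per arm is 80.0% at 20% v 10%, 89% at 25% v 12.5%, 95% at 30% v 15% and 99% at 37% v 18.5%. The shortfall therefore belongs to the fixed 10-point target.

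**The case against.** The strongest reply is that nothing was miscalculated. The 20% is openly an assumption, and no figure in the article contradicts it directly. Several parts of that reply stand.

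- **No composite rate is given.** A reader might infer that the article's own figures fix the control rate at 30% or more. They do not. The two-year figure covers aromatase-inhibitor users only and a longer window, and the 37% has no stated instrument or cut-off. The abstract's 30–40% stopping within five years would, under a constant hazard, give only 1 − 0.70^0.3 ≈ 10% to 1 − 0.60^0.3 ≈ 14% at 18 months. That illustration sits badly with 20% in the first year, so early stopping is probably faster, but it shows the spread.
- **The comparison crosses populations.** A composite is at least as frequent as one of its components in the same patients over the same period. Here the component comes from outside cohorts. The trial enrols consenting, digitally able patients at one centre with nurse support and an adherence notebook, so a lower control rate is possible. It cannot be said that the composite must exceed 20%. The link between the uncited 20% and the first-year figure is likewise an inference from the matching number.
- **The 41% adherent in the Singapore study.** It is tempting to read this as a 59% control rate. The article does not say how adherence was defined there, and in this trial a medium Morisky score is not a failure. That scenario is not used.
- **The drop-out inflation.** A reader might object that 438 less 10% leaves 394, below the required 398. Under the Statistical analyses section, however, every patient lost to follow-up is assigned an outcome, so none leaves the denominator.
- **The effect could be relative.** A halving would be well powered (step 5). But the article states no relative effect; its threshold is a difference of 10%, used as absolute.

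What remains is that a discontinuation rate is used, without justification, for a broader and later endpoint. Even the interpolated 25%, which counts discontinuation alone, takes power to 70.5% with 199 per arm.

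**Conclusion.** The point holds as an unjustified planning input, not as an arithmetic error. The stated 80% power for 10 points is tied to a narrower event than the primary endpoint. If the composite control rate is roughly 25–37%, power for a 10-point absolute difference is about 57–70% with 199 per arm, or 61–75% with 219 per arm before any dilution by imputation. The chance of missing a true 10-point benefit would be about 30–43% with 199 per arm, against the 20% planned. The difference detectable with 80% power would be about 11–13 points.

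This rests on three assumptions: that the Background cohorts are a fair guide to this centre's patients, that discontinuation can be interpolated between one and two years, and that the target is absolute. A reader might go further and call the trial inadequately powered outright. The article does not support that, because the true composite rate is unknown and a halving of failure would be detected with adequate power.

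**What to change.** Keep 438 patients and revise the sample size paragraph as follows:

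1. State an assumed 18-month control rate for the four-item composite and give its source, or say plainly that none exists and the rate is a judgement.
2. Use one term throughout for the event being sized, and say that the 10% is an absolute difference in percentage points.
3. Show power for 10 points, or the difference detectable with 80% power, over control rates of about 20–37%. Say whether the figures use 199 or 219 per arm and that they precede any effect of the imputation rule.
4. Note that power would be adequate if the application halved the failure rate.

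The cost is wording only: no extra patients and no change to the endpoint, the test or the conduct of the trial. The stated power becomes less favourable over most of the range.

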### Study experimental plan

The study will be proposed by breast nurses or physician oncologists to patients who meet the eligibility criteria. An explanation of the study and an information note will be given to them. Patients will be enrolled in the study once provided their written informed consent. Then, the randomization will be performed on the eCRF portal, stratified on the type of hormone therapy (Aromatase Inhibitor (AI) or Tamoxifen), as these treatments differ in terms of patients’ age at prescription, tolerance profile and adherence difficulties.

Patients will be assigned, according to a 1:1 randomization, to one of the following arms:

Experimental arm: WEBAPPAC web-application support (WEBAPPAC arm).Control arm: standard support.

The patients will be recruited over 30 months. Their participation will last 18 months.

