#### Statistical analyses

Exploratory analyses of the data will provide, for quantitative variables, the mean, standard deviation, median, quartiles, and number of missing values; for qualitative variables, we will calculate the frequencies and their 95% confidence intervals. The demographic and clinical characteristics of the patients will be described. An intent-to-treat analysis will be conducted. The statistical significance level is set at 5% for each statistical analysis and confidence interval.

The main objective is to compare the proportion of patients who had adherence failure 18 months after hormone therapy treatment start between the two groups. This comparison will be performed using a two-tailed Chi-squared test at the 5% level. All the measures will be used in order to reduce the number of patients lost to follow-up. For patients lost to follow-up at 18 months, with available data on adherence to hormone therapy at 6 months, data on adherence at 6 months will be retained, otherwise patients in the experimental arm will be considered as non-adherent and patients in the standard arm will be considered as adherent.

For secondary objectives, secondary endpoints will be described used the methods above described. The comparison of these endpoints between both groups will be performed using the Chi-squared test (or Fisher’s exact test if necessary) for qualitative variables, and through a Student’s test (or non-parametric Wilcoxon Mann Whitney test if necessary) for quantitative variables.

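### The stated 80% power takes no account of the primary rule for lost patients, which scores those without 6-month data in opposite directions in the two arms

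*Protocol article*

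**What the plan says.** The section Sample size determination of the Protocol article gives these elements:

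- Method: "According to a two proportion z-test", "with a two-sided alpha risk of 5% and a power of 80"%.
- Rates: "assuming an adherence failure rate of 20% in the control arm", with a "difference in discontinuation rate of at least 10"% as the target, i.e. 20% v 10%.
- Size before drop-out: "398 patients (199 per arm) are required".
- Size after drop-out: "To take into account a 10% drop-out rate, we plan to enroll 438 patients overall (219 per arm").

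The section Statistical analyses plans an intent-to-treat analysis with a two-tailed chi-squared test at 5%. It sets a two-step rule for patients lost to follow-up at 18 months. If adherence data exist at 6 months, that status is used; "otherwise patients in the experimental arm will be considered as non-adherent and patients in the standard arm will be considered as adherent".

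The sample size section does not carry this rule into the assumed rates. No section gives the share of patients expected to be lost without 6-month data.

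**The concern.** A drop-out inflation presumes that lost patients leave the analysis and that those who remain keep the assumed rates. The planned analysis does neither. Lost patients stay in the denominator, and those without 6-month data receive an outcome fixed by their arm: failure under the app, adherence under control. Each such patient raises the app arm's failure rate and dilutes the control arm's. The expected difference is then smaller than the 10 points on which the size rests.

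The article itself expects 10% drop-out, so the rule may apply to more than a stray patient. At stake is a trial described as having 80% power which, through its own scoring rule, could miss an app effect of exactly the size it was designed to find.

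**Working it through.** **Inputs from the Protocol article.** Failure 20% control v 10% app, two-sided 5%, 80% power, two-proportion z-test, 398 (199 per arm), 10% drop-out and 438 (219 per arm) come from Sample size determination. The 1:1 allocation comes from Study experimental plan. The scoring of lost patients comes from Statistical analyses.

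**Step 1: reproduce the base figure.** Pooled z-test without continuity correction, mean rate 0.15:

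n = [1.96 × √(2 × 0.15 × 0.85) + 0.8416 × √(0.20 × 0.80 + 0.10 × 0.90)]² / 0.10² = [1.96 × 0.50498 + 0.8416 × 0.5]² / 0.01 = 198.96

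This gives 199 per arm, 398 overall. The base figure is correct.

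**Step 2: the drop-out allowance.** 398 × 1.10 = 437.8, so 438. If 10% leave the analysis, 438 × 0.90 = 394.2, or 197 per arm, with power 79.6% against 80.0% at 199. The drop-out that 438 tolerates is 1 − 398/438 = 9.1%. Dividing instead gives 398/0.90 = 442.2, i.e. 443, or 444 with equal arms. The gap is 5 to 6 patients and 0.4 points of power.

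**Step 3: apply the planned scoring.** Let g be the share of randomised patients lost without 6-month data. This is an assumption, taken as equal in the two arms. All others are taken to fail at 20% and 10%, including lost patients whose 6-month status is carried forward. Then:

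- control rate = 0.20 × (1 − g)
- app rate = 0.10 × (1 − g) + g
- expected difference = 0.10 − 1.1 × g

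Power = Φ[(difference − 1.96 × SE₀) / SE₁], where SE₀ uses the pooled rate and SE₁ the two separate rates, with 219 per arm.

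Example at g = 2%: the rates are 0.196 and 0.118, and the difference is 0.078. SE₀ = √(2 × 0.157 × 0.843 / 219) = 0.0348. SE₁ = √[(0.196 × 0.804 + 0.118 × 0.882) / 219] = 0.0346. Power = Φ(0.285) = 61%.

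| g | Patients per arm (219 × g) | Control | App | Power |
|---|---|---|---|---|
| 0% | 0 | 20.0% | 10.0% | 83.7% |
| 0.4% | 0.9 | 19.9% | 10.4% | 79.9% |
| 1% | 2.2 | 19.8% | 10.9% | 73.5% |
| 2% | 4.4 | 19.6% | 11.8% | 61% |
| 3% | 6.6 | 19.4% | 12.7% | 48% |
| 5% | 11.0 | 19.0% | 14.5% | 24% |
| 10% | 21.9 | 18.0% | 19.0% | effect reversed |

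**Step 4: vary the carry-forward assumption.** Take 10% drop-out with every lost patient having 6-month data. If the 6-month failure rates are half the 18-month rates (10% v 5%), the arm rates become 0.9 × 20% + 0.1 × 10% = 19.0% and 0.9 × 10% + 0.1 × 5% = 9.5%, with power 81.4%. If no failures are recorded at 6 months, the rates are 18.0% and 9.0%, with power 78.9%.

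**Step 5: does a larger trial repair it?** With 222 per arm (444), power at g = 2% is 62% against 61% with 219. To restore 80% under the rule, with 6-month rates equal to 18-month rates, takes 257 per arm at g = 1%, 398 at g = 2.5% and 1080 at g = 5%.

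**The case against.** The strongest defence is that the arm-opposed scoring is only the second step. It applies to patients lost at 18 months who also have no 6-month adherence data. Table 2 schedules the adherence assessment at 6 months in both arms, the analysis section commits to limiting loss to follow-up, and Withdrawal from study says that patients who leave early go on being followed unless they refuse. If all drop-outs have 6-month data with rates like those at 18 months, all 438 are analysed at 20% v 10% and power is 83.7%, above the stated figure. The rule is also deliberately conservative: it works against the app, so a positive result would be the more convincing.

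Most of this stands. A reader might infer that the 80% power simply fails. The documents do not support that, because they give no share of patients lost without 6-month data. A reader might also infer that the trial is four patients short of 398 and that enrolling 444 would cure it. That does not follow either. The shortfall arises only if drop-outs leave the analysis, which the plan rules out; it costs 0.4 points of power, and 444 leaves the scoring problem almost untouched.

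What the defence does not remove is the narrow margin. About one patient per arm scored this way takes power below 80%, and the sample size paragraph does not mention it. Conservatism explains the direction of the rule but does not excuse a power figure that leaves it out. Both the power claim and the primary scoring rule are stated in the article, so this is not a detail left to a separate analysis plan.

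**Conclusion.** The concern holds in conditional form. The base size of 398 is right. The power attached to 438 does not describe the planned primary analysis, because it omits a scoring rule that shrinks the expected difference by 1.1 points for each 1% of randomised patients lost without 6-month data. The stated 80% survives only if nearly every drop-out has 6-month data and the 6-month failure rates are not far below the 18-month rates. The threshold is about 0.4% of randomised patients; 2% costs over 20 points of power, and 5% leaves about a quarter.

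These figures rest on an assumed share, on equal loss in the two arms, and, for the table, on 6-month rates equal to 18-month rates. Lower 6-month rates make the margin narrower still. The multiplication by 1.10 is a minor, separate slip.

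**What to change.** 1. Keep 438 and correct the sample size paragraph. For patients with observed outcomes, 438 tolerates 9.1% drop-out, or gives 79.6% power at 10%.
2. In the same paragraph, state the power under the primary scoring rule over a range of patients lost without 6-month data, for example 0% to 5%, with the carry-forward assumption named.
3. Preferably, use one rule for lost patients without 6-month data in both arms for the primary test, state the power under it, and keep the arm-opposed rule as a worst-case sensitivity analysis. If such patients receive the same status in both arms, whichever it is, the expected difference is 0.10 × (1 − g): 9.8 points at g = 2%, against 7.8 under the present rule.

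Raising enrolment to 444 should not be offered as the remedy.

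The cost is a change of text, a less favourable stated power and one extra sensitivity analysis. No additional patients are needed to state the figures correctly. Restating them does not, however, secure 80% power if the arm-opposed rule stays primary.

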#### Statistical analyses

Exploratory analyses of the data will provide, for quantitative variables, the mean, standard deviation, median, quartiles, and number of missing values; for qualitative variables, we will calculate the frequencies and their 95% confidence intervals. The demographic and clinical characteristics of the patients will be described. An intent-to-treat analysis will be conducted. The statistical significance level is set at 5% for each statistical analysis and confidence interval.

The main objective is to compare the proportion of patients who had adherence failure 18 months after hormone therapy treatment start between the two groups. This comparison will be performed using a two-tailed Chi-squared test at the 5% level. All the measures will be used in order to reduce the number of patients lost to follow-up. For patients lost to follow-up at 18 months, with available data on adherence to hormone therapy at 6 months, data on adherence at 6 months will be retained, otherwise patients in the experimental arm will be considered as non-adherent and patients in the standard arm will be considered as adherent.

For secondary objectives, secondary endpoints will be described used the methods above described. The comparison of these endpoints between both groups will be performed using the Chi-squared test (or Fisher’s exact test if necessary) for qualitative variables, and through a Student’s test (or non-parametric Wilcoxon Mann Whitney test if necessary) for quantitative variables.

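### Randomisation is stratified by hormone-therapy type but the primary chi-squared test ignores the stratum; this gives up a little power only if failure differs substantially by type

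*Protocol article*

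**What the plan says.** The section on the study experimental plan states that randomisation is "stratified on the type of hormone therapy (Aromatase Inhibitor (AI) or Tamoxifen"). The reason given is that the two treatments differ in "age at prescription, tolerance profile and adherence difficulties". The primary endpoint is itself an adherence measure: the proportion of patients with adherence failure within 18 months.

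Under Statistical analyses the primary comparison is fixed in one sentence: "This comparison will be performed using a two-tailed Chi-squared test at the 5% level". No stratification or adjustment is attached to it.

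The sample size section uses the matching unstratified method. It begins "According to a two proportion z-test", continues "with a two-sided alpha risk of 5% and a power of 80" per cent, "assuming an adherence failure rate of 20% in the control arm", and concludes that "398 patients (199 per arm) are required".

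The article gives neither the expected AI/tamoxifen split nor a failure rate for either type.

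**The concern.** The protocol's own reason for stratifying implies that hormone-therapy type may predict the primary outcome. Stratified allocation balances type across the arms, so differences between types no longer add to the variance of the treatment comparison. The pooled variance in an ordinary chi-squared test still contains that between-type component. If type is prognostic, the test's standard error is too large, its true type I error falls below 5%, and it detects a real effect slightly less often than a test that uses the stratum. What is at stake is efficiency, and consistency between design and analysis.

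**Working it through.** **1. The plan's own figure.** Inputs from the sample size section: 20% versus 10%, two-sided 5%, 80% power. With pooled variance and mean rate 0.15:

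n per arm = [1.960 × √(2 × 0.15 × 0.85) + 0.8416 × √(0.20 × 0.80 + 0.10 × 0.90)]² / 0.10²
= (0.9897 + 0.4208)² / 0.01 = 198.96, rounded up to 199.

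This reproduces 199 per arm and 398 overall. The enrolled 438 is 398 × 1.10. The calculation matches the unstratified test named in the analysis section.

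**2. How the crude test becomes conservative.** Let w be the AI share and g the gap in failure rate between types. With no treatment effect and an overall rate of 20%, the crude variance per patient is 0.20 × 0.80 = 0.16. The part that stratified allocation removes is w(1 − w)g². The true standard error is therefore the nominal one times √[(0.16 − w(1 − w)g²)/0.16]. For w = 0.5:

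- g = 0.10: √(0.1575/0.16) = 0.992; effective critical value 1.960/0.992 = 1.976; alpha about 4.8%.
- g = 0.20: √(0.1500/0.16) = 0.968; critical value 2.024; alpha about 4.3%.
- g = 0.30: √(0.1375/0.16) = 0.927; critical value 2.114; alpha about 3.5%.

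**3. Simulation at the planned rates.** 400,000 trials per scenario, 199 per arm, 1:1 within two strata. Overall failure is held at 20% (control) and 10% (experimental), with a common odds ratio across types. The comparison is Pearson chi-squared against Cochran-Mantel-Haenszel (CMH) without continuity correction. The AI shares (50%, 65%, 80%) and all gaps are assumptions.

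| Gap between types (points) | Crude alpha | Crude power | CMH power | Power given up by crude test (points) |
|---|---|---|---|---|
| 0 | 5.0–5.1% | 80.9–81.0% | 80.6% | none (crude higher by about 0.4) |
| 5 | 5.0–5.1% | 80.8–80.9% | 80.7% | none (crude higher by 0.1–0.2) |
| 10 | 4.8–5.0% | 80.8–80.9% | 80.9–81.1% | 0.1–0.2 |
| 15 | 4.6–4.8% | 80.8–81.0% | 81.3–81.7% | 0.5–0.7 |
| 20 | 4.4–4.6% | 80.9–81.2% | 81.8–82.5% | 0.9–1.4 |
| 30 (AI share 50% or 65% only) | 3.5–3.6% | 81.5–81.7% | 84.2–84.7% | 2.6–3.0 |

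A 30-point gap is impossible at an AI share of 80%, because it would need a negative tamoxifen rate (0.20 − 0.80 × 0.30 = −0.04). CMH alpha was about 5% throughout.

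These losses are slightly on the high side. In a stratum of odd size, the simulation always placed the extra patient in the same arm, which costs the crude test a little. Placing that patient at random (1,000,000 trials per scenario) gives losses within 0.1 of zero at a gap of 10, about 0.6–1.1 at 20 and about 2.1–2.5 at 30.

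**4. Other rates.** 219 per arm, strata 60/40, rates assumed:

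- Control failure 12% and 32% by type (0.6 × 12 + 0.4 × 32 = 20%), halved by the application: alpha about 4.3% crude versus 5.0% CMH; power about 85.0% versus 85.9%.
- Control failure 25% and 55% (0.6 × 25 + 0.4 × 55 = 37%), 10-point effect: alpha about 4.1% versus 5.0%; power about 61.6% versus 65.8%, a loss of about 4 points.

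**The case against.** The strongest case against acting is that nothing the plan promises is lost. The trial was sized for the same unstratified test that it will use, 199 per arm reproduces, and the crude test kept about 81% simulated power in every scenario at the planned rates. Any loss depends on a gap between types that the documents do not quantify; an expectation of differing adherence difficulties says nothing about its size. The 4-point figure needs a 30-point gap and an average control rate of 37% instead of the planned 20%. All of this stands, and it limits the point to a small, conditional gain in efficiency.

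The 37% scenario still deserves a place. The planning rate of 20% is taken from discontinuation, whereas the endpoint also counts low Morisky scores, and the Background cites a study with 37% poor adherence. It shows sensitivity to a higher rate; it is not a forecast.

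A reader might infer that an unstratified test after stratified randomisation is invalid, or that the trial is underpowered because of it. Neither follows. The error is on the conservative side, and the sample size calculation and the test agree with each other.

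The analysis plan is not shown and may contain a supportive stratified or adjusted analysis; its absence from the article is no finding. The primary test, however, is stated outright in the article, so the mismatch is in the text.

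**Conclusion.** The mismatch between design and primary test is real, and its consequence is minor. If failure differs substantially by type, the crude test is mildly conservative. At the planned 20% versus 10%, the power given up is about nil for gaps up to 10 points, about 1 point at 20 (alpha about 4.4%) and at most about 3 points at an extreme 30. At control rates of 25% and 55% by type it is about 4 points. Every stratum rate and AI share behind these figures is an assumption. The reading that the test is conservative and loses power whatever the data goes too far: with no gap between types there is nothing to recover. The validity of the test and the stated 398 and 438 patients are unaffected.

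**What to change.** Make the primary test a Cochran-Mantel-Haenszel test stratified by AI/tamoxifen as recorded at randomisation. Report the Mantel-Haenszel risk difference with its 95% CI as the effect estimate, and keep the crude chi-squared test as a supportive analysis. Fix the change before any outcome data are seen, since a later switch would look data-driven.

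The cost is a short change to the analysis text, made through a documented amendment because the primary test is already stated. No further patients or data are needed, since the stratum is already collected. The statistical downside is practically none: if type is not prognostic, the stratified test has a few tenths of a point less power at most (80.6% versus about 81.0% at 199 per arm).
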